### Interventions

All participants will be educated on the nature of their pathology, the rationale for exercise treatment, the importance of adherence to their home program as well as activities to avoid (ascending and descending stairs, sitting in low chairs, lying on hip during sleep). They will be provided an information booklet that includes this information. The booklet details pain relieving postural strategies (standing, sitting and lying/sleeping) to adopt during the 12-week intervention. Participants may apply an ice pack to the lateral hip region at any time; are encouraged to stay active within their pain limits and to continue their normal pain medication regime during the 12-week intervention. Both medication use and ice application will be recorded throughout the trial in the participant’s exercise/transdermal cream application diary. All participants are able to continue normal daily activities but will be asked to identify any medication usage for their tendinopathy (e.g. NSAIDs) and cease any other physical treatment (physiotherapy, etc.).

#### Exercise therapy

Both exercise therapy groups will complete a 12-week exercise program prescribed by a physiotherapist. Participants in both groups will attend a physiotherapy consultation at baseline, 4-weeks, 8-weeks and 12-weeks post randomisation for progression of their exercise program and monitoring of adherence. A booklet that features photos and explanations of each exercise will be given to each participant for further reference and participants are invited to contact their physiotherapist at any time during the 12 week intervention if they have queries about their cream or exercise program. Before, during and after the 12 week program, participants are invited to contact the researchers with any questions about the trial. Two cycles of the exercise program will be completed twice daily (AM and PM). Both programs should take approximately 15 min to complete.

#### Gluteal La Trobe trial (GLoBE) protocol/intervention exercise therapy

Participants randomised into the intervention exercise group will be instructed in the GLoBE protocol, a gluteal tendon exercise program designed by clinicians who are expert in treating tendon pathology. Although numerous rehabilitation exercises (eccentric [32, 48], concentric [30, 49] and isometric [50]) have been described for the management of Achilles and patellar tendinopathy, there is little evidence on effective exercise therapy in the rehabilitation of GTPS [37]. There is evidence that the use of isometric exercises may reduce tendon pain in the initial stages of rehabilitation [50] and allow the continuation of sporting activities [51]. This pain relief may provide a window of opportunity for lower limb strengthening with isotonic exercise. The effectiveness of isometric exercises is yet to be validated in the GTPS population. The GLoBE protocol largely focuses on isometric loading of the gluteus medius and minimus, and strengthening of the kinetic chain – quadriceps and calf muscle groups. It is a graduated exercise program where participants are able to progress through the stages in each subsection of gluteal, quadriceps and calf strengthening. The gluteal strengthening commences with a hip hitch in standing, whereby the participant, holding onto a wall or chair for balance, hitches their unaffected leg up off the ground (approximately 1 cm) whilst keeping their knee in full extension, causing the contralateral/affected gluteal tendons to be loaded out of a compressed position. This hip hitch is then integrated into dynamic exercises by adding a toe taps or hip swings as progressions. The most advanced exercise in the gluteal series, is a single leg wall squat. Quadriceps strengthening commences with a double leg ¼ squat and progresses to a ½ squat, sit to stand exercise and then to step ups. Calf strengthening involves double leg calf raises, calf raises with toe taps and progresses onto single leg calf raises.

#### Sham exercise program

The control group will receive a sham exercise program not suitable for the rehabilitation of gluteal tendons, instructed by a physiotherapist. Like the GLoBE protocol, the program is completed as a cyclic three-stage approach, where participants are able to progress through each subsection of sham gluteal, quadriceps and calf strengthening. The sham program involves exercises for the kinetic chain in an unloaded environment (sitting) and thus, does not therapeutically load the gluteal tendons.

### Physiotherapy treatment integrity

A variety of methods will be used to ensure the integrity of the exercise intervention is maintained. All treating physiotherapists will have a minimum of 2 years clinical experience in private musculoskeletal physiotherapy practice and will undertake a compulsory 1 day training course. This will incorporate extensive education about GTPS, a step-by-step approach to the two exercise interventions and guidelines on trial reporting (participant adherence, adverse events, and clinical note taking). The education session will include group discussions and portions of experiential learning such as patient role play and formal clinical mentoring as outlined by Main et al., [47] for training physiotherapists delivering interventions. Regular phone and email contact with the researchers and provision of a comprehensive treatment manual will aim to maximise therapist adherence to the protocol. Additionally, a large emphasis will be placed on the importance of equal service provision and standardisation of enthusiasm of both exercise protocols [52, 53].

Physiotherapists will use structured electronic recording forms for sham and intervention exercise programs. These will include a series of check boxes to prompt the clinician through each stage of the program and to ensure standardisation of treatment intervention. Additionally, the physiotherapist will be instructed to record exercises prescribed, adherence, use of pain or NSAID medications and/or ice application and any adverse events. These measures adhere to the recommended requirements for ensuring treatment fidelity [47]. Clinical notes will be audited by research staff at 4-weeks and 12-weeks to ensure that all documentation is standardised, legible and complete.

### Transdermal cream

All participants will be required to apply 1 g of the compounded transdermal cream daily to thin-skin areas of the body to aid absorption and rapid distribution of active ingredients. Cream application sites will be rotated every 5 days – alternating between the inner right wrist and the inner left wrist. Rotation of sites every 5 days will reduce the likelihood of up-regulation of receptors [54]; skin sensitivity by constant application to the same area and undesired build-up and delayed uptake of active ingredients [55]. Participants will be advised to not to rub in too hard, but simply to spread the gel over the skin as thinly as possibly to optimise absorption [56].

Both the placebo and intervention transdermal creams will be applied using a metered dose pump dispenser manufactured by Medisca, a Therapeutic Goods Administration (TGA) registered supplier of pharmacy compounding products. This dispenser accurately delivers the required dose (1 ml) in one pump (mean error = 0.056 ml, relative SD = 4.4 %) [57]. Both intervention and placebo groups will receive an identical instruction sheet for the application of the cream. The method of application will also be reinforced verbally by the physiotherapist in the first exercise treatment session. Any significant or severe adverse reactions will immediately be referred to a medical practitioner or emergency department for assessment.

#### Menopausal hormone therapy transdermal cream

The MHT cream is based on the active ingredients used in the Estalis Continuous transdermal patch [58]. Cream application will involve transdermal delivery of supplementary oestradiol (50mcg) and norethindrone acetate (NETA) (140mcg), a progestin, in a VersaBase® for 12 weeks in duration. This is likely to increase serum levels of E_2_, with an aim to reach an optimum level of 295–550pmol/L [54]. The progestin component provides essential protection of the uterus to reduce the risk of endometrial hyperplasia [59].

#### Placebo transdermal cream

The placebo transdermal cream, applied for a duration of 12 weeks, will be an inert aqueous transdermal cream that is identical in colour, texture and consistency to that of the MHT cream but without the active ingredients.

### Baseline assessments

At baseline, a thorough medical history will be taken, time-interval since menopause documented and current medication use and dosage will be recorded. Height and weight will be measured using a stadiometer and digital scales, respectively, and body mass index will be calculated as weight (kg)/height (m)^2^. In addition, six questionnaires will be administered to monitor pain, function and quality of life.

#### Secondary outcome measures

Secondary outcome measures will include five questionnaires to assess pain and dysfunction. The following questionnaires will be administered at baseline, 12-weeks and 52-weeks: Oxford Hip Score (OHS) [63], global rating of change questionnaire, Assessment of Quality of Life (AQoL), Hip dysfunction and Osteoarthritis Outcome Score (HOOS) [64] and the Lateral hip Pain Questionnaire (unpublished, University of Queensland, Australia).

### Failure to improve

Participants will be offered cross over to both active interventions if their global rating of change score is below 0 (worsened symptoms) at 12 weeks. If in GLoBE exercise and placebo cream, they will cross over to intervention cream and continue GLoBE exercise. If in sham exercise and placebo cream, they will cross over to GLoBE exercise and intervention cream, if in sham exercise and intervention cream, they will cross over to GLoBE exercise and continue intervention cream once cleared to do so by study medical practitioners. Results for this group will be analysed and presented separately.

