#### Blood sampling and electrocardiography

Participants who remain eligible for the study following medical consult, will be referred for blood tests and an electrocardiograph to confirm eligibility in the trial. Blood tests will examine lipid levels (fasting cholesterol, triglycerides, high density lipoprotein: HDL, low density lipoprotein: LDL), liver function (LFT), diabetes indicators (glucose, HbA1c), iron (Fe) studies and thyroid function (TFT). Serum levels of follicle stimulating hormone (FSH) and oestradiol will also be recorded as a baseline measure and compared to levels post pharmacological intervention. A 12 lead echocardiograph (ECG) will be undertaken to monitor if any arrhythmia or irregularities are present. Indicators for inclusion or exclusion of a participant will be made on clinical judgement by the treating physician, taking into account all individual tests results and their normative values.

Once deemed eligible for the trial, participants will be randomly allocated into an exercise group and a transdermal cream group. A participant may be randomised into one of the following 12-week interventions: (i) exercise therapy, placebo cream; (ii) sham exercise, MHT cream; (iii) sham exercise, placebo cream or (iv) exercise therapy, MHT cream.

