### Statistical analysis

Statistical analysis will use intention to treat principles and per protocol analysis. A mixed model ANCOVA will be undertaken, adjusting for baseline values of the dependent variables to determine the difference between groups for primary and secondary outcomes. In addition, a responder analysis will be undertaken to determine clinical significance [65]. Participants who achieve an increase in VISA-G scores greater than the minimal detectable change score (10 points) [60] will be categorised as responders. The difference between the proportions of responders and non-responders in the four groups will then be analysed with risk ratios, risk differences and numbers needed to treat [53]. Participants randomised into the single exercise arm will be analysed separately. Where data is missing, baseline data will be carried forward.

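### Women who worsen and cross over at 12 weeks are to be analysed separately, with nothing said to keep them in their randomised arm at 52 weeks, which conflicts with the promised intention-to-treat analysis

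*Protocol article*

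**What the plan says.** All references are to the protocol article.

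- **Trigger (Failure to improve).** Participants are "offered cross over to both active interventions if their global rating of change score is below 0". The rating is taken at 12 weeks, so it is an outcome observed after randomisation.
- **Routes (same section).** Three are listed. For women on active exercise with placebo cream the text reads: "If in GLoBE exercise and placebo cream, they will cross over to intervention cream and continue GLoBE exercise". Women given both control components switch both. Those given sham exercise with the hormone cream switch only the exercise.
- **The fourth arm.** The Blood sampling and electrocardiography section lists the randomised combinations, ending with "iii) sham exercise, placebo cream or (iv) exercise therapy, MHT cream". The combined arm already has both active interventions and has no route.
- **Handling of results (Failure to improve).** "Results for this group will be analysed and presented separately".
- **Analysis principle (Statistical analysis).** "Statistical analysis will use intention to treat principles and per protocol analysis". The Abstract also commits to intention to treat, and the Discussion names it as one of the features that limit bias.
- **Timing (Primary outcome measures).** VISA-G is recorded at baseline, 12 weeks and 52 weeks, so the last measurement comes after any cross-over.

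**The concern.** Intention to treat at 52 weeks means comparing everyone randomised, in the arms to which they were randomised. A rule that sets women aside because of how they felt at 12 weeks does something else. It conditions the comparison on a result that treatment may itself have influenced.

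The rule is also lopsided. Women who worsen on sham plus placebo, exercise plus placebo or sham plus MHT can cross over and be set aside. Women who worsen on the combination have no route and, as far as the text goes, stay in their arm. Three arms would be cleared of some of their poorer 12-week responders and the fourth would not. The combination is part of the title question, and the tendency is to make it look less beneficial at 52 weeks than it is. The factorial main effects are touched too, because the combined arm is half of the active side of each.

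**Working it through.** **Setting the sections side by side.** Failure to improve states a rule for women who cross over. Statistical analysis states a principle for all randomised women. No sentence links them: none says that the separate results are additional, and none confines the separation to the per-protocol analysis. Statistical analysis also sets the exercise-only participants apart for separate analysis, and those women do stand outside the four-group comparison. An analyst reading the article would probably treat women who cross over in the same way.

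**The plan's own figures.** The article gives no figure for cross-over. The inputs borrowed from Sample size and power analysis are SD 13 and a target difference of 10 points. With these, the two-sided normal formula gives n = 2 × (13 × (1.960 + 0.842) / 10)² = 26.5, so 27 per group, against the stated 25. That is a separate matter and nothing below depends on it.

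**Inputs not in the article (assumed).**
- Share p of an arm that worsens and crosses over: 10–20%, which is 2.5 to 5 women out of 25.
- Correlation r between 12-week status and 52-week VISA-G: 0.3–0.7.
- Normal outcomes, with the women who cross over being the lowest p at 12 weeks.
- No effect of the cross-over treatment.

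**Shift in one affected arm.** Removing the lowest share p at 12 weeks raises the 52-week mean of those who remain by

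shift = r × SD × φ(z_p) / (1 − p).

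- p = 0.10: 13 × 0.1755 / 0.90 = 2.53; times r = 0.3, 0.5, 0.7 gives 0.76, 1.27, 1.77 points.
- p = 0.20: 13 × 0.2800 / 0.80 = 4.55; times r = 0.3, 0.5, 0.7 gives 1.36, 2.27, 3.18 points.

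The range is about 0.8 to 3.2 points, or 8–32% of 10. At p = 0.05 and r = 0.3 it is only 0.42.

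**Effect on the contrasts.** Let each of the three affected arms shift by d and the combined arm by 0.
- Combined versus any one other arm: 0 − d = −d.
- Exercise main effect: (d + 0)/2 − (d + d)/2 = −d/2, or about −0.4 to −1.6 points. By symmetry the MHT main effect has the same bias.
- Between two of the three affected arms, equal shifts cancel.

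**Simulation check** (25 per arm, 3,000 runs per scenario, p = 10–20%, r = 0.5–0.7, combined versus sham plus placebo):

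| True difference | Everyone kept | Cross-overs removed from three arms |
|---|---|---|
| 0 | about 0 | −1.3 to −3.2 |
| 10 | about 9.9 | 8.6 down to 6.7 |
| Power at 10 | 0.75–0.76 | 0.62 down to 0.42 |

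The simulated exercise main effect under no true difference was −0.7 to −1.6, in line with −d/2.

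**If these women were treated as missing instead.** Statistical analysis carries baseline forward where data are missing. A woman who had worsened would then be scored as unchanged, while worsening in the combined arm would stay as observed. The imbalance points the same way.

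**The case against.** **Exclusion is not stated.** The sentence says the results are shown separately. It does not say the women leave the main comparison, and intention to treat is promised three times. A separate table is compatible with keeping everyone in her arm. The parallel with the exercise-only participants is imperfect, since they were never randomised to a cream. This stands: removal is the plain reading, not the literal one. A reader might infer that the article openly abandons intention to treat, and it does not go that far. Nor is this just a detail left to a fuller document: the article states a rule, and read plainly that rule conflicts with another it states.

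**The combined arm is not addressed.** The article does not say how women who worsen on the combination are handled. If they were set apart too, the imbalance in form would go. The comparison would still be conditioned on a 12-week outcome that may differ by treatment.

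**These may not be the worst 52-week outcomes.** A reader might infer that the rule discards the poorest 52-week scores. The documents do not support that. The trigger is a self-rating at 12 weeks, and women who accept receive both active interventions before the 52-week measurement.

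**The size could be pushed too high.** A correlation of 1 gives 4.55 points at 20%, about 46% of the target. A transition rating will not predict a score 40 weeks later perfectly, so that is not a credible bound. Cross-over is only offered, and medical clearance is mentioned, so uptake may be partial.

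**Intention to treat has its own distortion.** If cross-over works, keeping these women in their arms narrows the 52-week difference. If those who cross over gained 10 points, an arm's mean would rise by 0.10 × 10 = 1 to 0.20 × 10 = 2 points, similar in size to the selection shift. This stands. The case for intention to treat is that it compares randomised groups and has a defined meaning, not that it recovers the effect without cross-over.

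**Conclusion.** The point holds as an unreconciled conflict between Failure to improve and Statistical analysis, confined to 52 weeks. Followed on its plain reading, the separate-analysis rule makes the 52-week comparison non-randomised and tends to bias the combination toward no benefit. That conclusion is structural and needs no numerical assumption beyond some women crossing over and 12-week status carrying some information about 52 weeks.

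The size does rest on assumptions. With SD 13 from the article, and assuming 10–20% crossing over, a correlation of 0.3–0.7 and no effect of the cross-over treatment, the shift is about 0.8–3.2 points for the combined arm against one other arm. It is about half that for the exercise main effect. The 12-week comparison need not be affected, because cross-over follows that assessment.

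**What to change.** Reconcile the two sections with three statements:

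1. Every randomised woman is analysed in her allocated arm at 52 weeks, whether or not she crossed over.
2. The separate results for women who crossed over are supplementary and descriptive.
3. The 52-week result is the effect of initial allocation, including any later cross-over.

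None of this changes who is offered cross-over or what they receive. It needs no new data, because 52-week questionnaires are already planned.

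The cost is that the 52-week difference may be diluted by cross-over and must be labelled so wherever it is reported.

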### Trial follow-up

At 52-weeks, participants will be asked to complete the six questionnaires again, and asked to specify if they continued any hormone therapy interventions or had any form of injection (cortisone, protein-rich-plasma or autologous blood injections) or surgical procedure post-trial.

### Success of blinding

To assess the effectiveness of blinding and to ensure participant expectation effects were protected, participants will be asked at one-week post intervention if they know which group they have been randomised to with the following two questions: “This trial compares the effect of two exercise programs, a new program and a standard program. Are you aware of which exercise program you received?”; “This trial compares the effect of two transdermal creams, a hormone therapy cream and a placebo cream. Are you aware of which transdermal cream you have received?” For both questions, the participant can answer with “yes”, “no” or “unsure”. If the participant answers “yes” the participant will be further questioned “which exercise program/cream do you think you received?” and “why” [46].

### Adverse events

Complications and adverse events associated with the intervention are unlikely, however, minor, significant and severe adverse events for this trial are based on the MIMS Australia Estalis Continuous (oestradiol/NETA: norethisterone acetate) consumer information sheet [58]. All adverse events will be recorded in the clinical notes, significant events referred to the treating medical practitioners and severe events referred to the emergency department. Significant and severe adverse events will be reported to the La Trobe University Human Ethics Committee, Faculty of Health Sciences using a standardised form. A participant has the right to withdraw from the study at any time.

*Minor Adverse Event:* Refers to any symptom or event reported by the participant that may be potentially related to the intervention. This will include:irregular vaginal bleeding or spottingtender, painful or swollen breastsmenstruation-like painredness, irritation or itching at the site/s of cream applicationskin rashvaginal itching, inflammation or fluid dischargeswelling of the lower legs, ankles, fingers or abdomen due to fluid retentionnausea, abdominal cramps, vomiting, heartburn, wind, diarrhoeaheadache, migrainerise in blood pressureweakness or dizzinessdepression, nervousness, rapid changes in mood, difficulty sleepingback painchange in sex driveweight gainacne, itchy or dry skin, skin discolourationdarkening of the skin particularly on the face or abdomen (chloasma)hair loss

*Significant Adverse Event:* Any symptom or event potentially related to the intervention that interrupts the participant’s ability to continue with the RCT intervention, or requires the participant to be referred to a medical practitioner. This will include:heavy vaginal bleedingpain or tenderness in the abdomen, which may be accompanied by fever, loss of appetite, nausea and vomitinga yellow colour to the skin or eyes, itching, dark coloured urine or light coloured bowel motions

*Severe Adverse Event:* Any symptom or event potentially related to the intervention that results in admission to the hospital, or permanent disability, or is life threatening. This will include:swelling of the face, lips, tongue, the area around the eyes or other part of the bodyrash, itching, hives, breathlessness or difficult breathing, wheezing or coughinglight-headedness, dizziness, changes in levels of consciousness, hypotension, with or without mild generalized itching, skin reddeningsigns that blood clots may have formed, such as sudden severe headache, sudden loss of coordination, blurred vision or sudden loss of vision, slurred speech, numbness or tingling in an arm or leg, painful swelling in the calves or thighs, chest pain, difficulty breathing, coughing blood

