### Randomisation, allocation and blinding

A block randomisation schedule will be generated using a web based randomisation program (https://www.randomizer.org/) with the sequence tranferred onto a computer spreadsheet by a researcher external to the trial investigators, who will have no contact with participants throughout the duration of the trial. This external researcher will complete concealed allocation of participants to groups in accordance with the randomisation schedule. All data collected will be de-identified and only made accessible to the study investigators.

Participants will be blinded to allocation for both the exercise therapy and hormone therapy group. Placebo creams and sham exercise groups, may increase the success of participant blinding [46]. The success of blinding will be formally measured during week 1 of the trial by asking participants to indicate which group for both interventions they believe they are allocated to. It is important to assess the success of blinding to determine if protection against participant expectation effects is maintained [46]. The treating physiotherapists will be blind to cream type, but due to the nature of the intervention, cannot be blinded to exercise group. Detailed training of physiotherapists will be provided to ensure equivalent provision of care and motivation for both groups [47]. Unblinding of a participant and trial investigators to cream allocation will only be permissable in the unlikely event of an adverse reaction requiring medical team involvement.

Data analysts and outcome measure assessors will be blinded to group allocation. This will be achieved through direct communication from the external researcher preparing the randomisation schedule to the trial physiotherapist implementing the exercise intervention and the pharmacist implementing the hormone cream intervention.

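### All three adverse-event classes require possible relatedness, so an admission or death judged unrelated has no class and no stated route to the ethics committee; death is also not named

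*Protocol article*

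**What the plan says.** The Adverse events section of the protocol article sets up three classes, and each one has possible relatedness in its definition.

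- Minor: "Refers to any symptom or event reported by the participant that may be potentially related to the intervention".
- Significant: "Any symptom or event potentially related to the intervention that interrupts the" participant's continuation in the trial, or leads to a medical referral.
- Severe: "Any symptom or event potentially related to the intervention that results in admission to the hospital, or permanent disability, or is life threatening".

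Each definition is followed by a list of symptoms, drawn from the consumer information for the hormone product on which the cream is based.

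The same section states "All adverse events will be recorded in the clinical notes". For oversight it states "Significant and severe adverse events will be reported to the La Trobe University Human Ethics Committee".

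Physiotherapy treatment integrity gives the recording task to the treating physiotherapists: "the physiotherapist will be instructed to record exercises prescribed, adherence, use of pain or NSAID medications and/or ice application and any adverse events". Randomisation, allocation and blinding says these physiotherapists are blind to the type of cream but "cannot be blinded to exercise group".

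**The concern.** Two rules in the plan do not fit together. The recording rule covers all events, whereas the classification rule covers only events thought possibly related. Ethics reporting depends on the classification, so the narrower rule decides what the committee sees.

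Relatedness is a judgement, and in a small trial of a hormone preparation an early judgement may prove wrong. If it decides whether an event is classified at all, rather than being one attribute of a classified event, a serious event first thought unrelated has no stated route to oversight. Any comparison between arms that used the classified events would also depend on that judgement. Judgement made with knowledge of allocation can differ between arms without any true difference in event rates.

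**Working it through.** The plan gives no figure on this point, so there is nothing to recompute. The check is to read the rules together and follow example events through them.

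**The rules**

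| Class | Relatedness required? | Further criterion | Reported to ethics committee? |
|---|---|---|---|
| Minor | Yes | Reported by the participant | No |
| Significant | Yes | Interrupts participation or needs medical referral | Yes |
| Severe | Yes | Hospitalisation, lasting disability or threat to life | Yes |

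The recording sentence in Adverse events and the instruction to physiotherapists have no relatedness condition.

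**Example events**

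1. *Admission judged possibly related.* It is recorded, classed as severe and reported. The rules work.
2. *Admission judged unrelated.* It fails the severe definition on relatedness, and the other two classes for the same reason. It has no class, and the ethics reporting sentence does not reach it.
3. *Death judged unrelated.* As in example 2: no class and no stated route.
4. *Sudden death outside hospital, judged possibly related.* Death is not among the severe criteria. The event is covered only by inference, through the criterion on threat to life.

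**Does the recording sentence close the gap?** It can be read in two ways.

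- *Broad:* every event is written in the notes, and the classes govern grading, referral and reporting. Examples 2 and 3 are then in the notes but remain unclassified and unreported.
- *Narrow:* the sentence means all events within the three classes, the only adverse events the section defines. Examples 2 and 3 then need not be recorded at all.

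The reporting gap remains under both readings. Only the broad one preserves the data.

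**Where could knowledge of allocation enter?** The physiotherapists record events and know the exercise programme but not the cream. Any effect of allocation knowledge through them can therefore touch GLoBE versus sham exercise, but not hormone cream versus placebo. The symptom lists offer little restraint on the exercise contrast, because they come from hormone product information and, back pain apart, contain almost nothing specific to exercise.

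**The case against.** The strongest reply has five parts.

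- **The threshold is low.** Possible relatedness is an inclusive standard, and the symptom lists limit discretion for what they name. This stands, and it suggests few events would be lost. It does not help an admission or death from a cause outside the lists.
- **Recording is unfiltered.** Two sentences cover all or any events, and clinical notes are audited at 4 and 12 weeks. This stands to the extent that loss of data is not established. It does not supply a class or a reporting route.
- **A reader might infer that unblinded therapists make the causality judgement.** The document does not say so. It gives them recording, sends significant events to the treating medical practitioners and severe events to the emergency department, and names no assessor. A fuller protocol may name one, so the absence of a name is not itself the finding.
- **A reader might infer that the hormone safety comparison is biased.** The documents do not support this. The physiotherapists are blind to cream, and the Statistical analysis section describes between-group analysis of primary and secondary outcomes only. No between-arm safety comparison is specified that could be called biased.
- **A fatal event would often first meet the admission or life-threatening criterion.** This is fair, and it reduces the missing word to a gap in wording. The gap still matters for sudden death outside hospital.

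**Conclusion.** The point holds as a conflict between stated rules. The relatedness condition in all three definitions is explicit text, not a detail left to another document. Combined with class-based ethics reporting, it leaves any admission or death judged unrelated without a class or a stated reporting route. This follows from the definitions and needs no assumption.

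The size of any bias cannot be given. The document states neither an event rate nor how often relatedness would be judged differently by arm, and a ratio built on invented values would only restate them. What can be said is conditional: if knowledge of exercise allocation influences relatedness through the recording physiotherapists, it would bias any GLoBE-versus-sham comparison of classified events. Through them, the cream contrast is not exposed.

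The omission of death is a smaller matter of wording. The change is worth making because it is cheap and because events never classified or reported may be hard to recover later.

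**What to change.** For recording, classification and ethics reporting:

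1. Remove the relatedness condition from the minor, significant and severe definitions, and define each by severity or consequence alone.
2. Name death in the severe class.
3. Add relatedness as a separate field on the existing electronic recording form, preferably completed by an assessor blind to both the exercise and the cream allocation.
4. Tabulate all events by arm, with related events as a subset.

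Leave the clinical referral rules as they are, apart from reconciling their wording with the revised definitions.

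The cost is a wording change, one extra field and a few more events to classify and report. Treatment, visits and sample size are unaffected.
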